### Control group

The 13 departments randomized to the control group will not receive any intervention, and will be encouraged to continue their normal working procedures throughout the study period.

### Process evaluation

Through process evaluation we aim to: 1) document if the different parts of the interventions are actually implemented, 2) follow the change process, as well as 3) detect and understand eventually divergent activities and unexpected outcomes. The process evaluation framework used in this study is inspired by different process evaluation approaches [35–37], which partly overlap but also focus on specific aspects only represented in one or two of these approaches. The approach developed by Saunders et al. (2005) focusses primarily on aspects that help to document the degree of implementation, i.e. to what degree the intervention was implemented as planned. It consists of the following aspects: fidelity (extent to which the intervention was implemented according to the principles of the intervention), dose delivered (amount or number of intended units of each intervention or component delivered or provided by interventionists), dose received/exposure (extent to which participants actively engage with, interact with, are receptive to, and/or use materials or recommended resources), dose received/satisfaction (participants satisfaction with program, interactions with staff and/or investigators), reach (participation rates of the different activities), recruitment procedures used to approach and attract participants at individual or organizational levels, context (aspects of the environment that may influence intervention implementation or study outcomes).

The model of Nielsen and Randall (2013) overlaps partly with the aspects from the Saunders approach, but also adds important components, for example the aspect of “mental models”, i.e. the participants’ attitudes to the intervention before and under the intervention (e.g. readiness for change) which we consider particularly important for the understanding of participatory interventions [38]. In addition, the framework developed by Fridrich et al. (2015) overlaps with the other two approaches, but adds a more thorough evaluation of context that goes beyond a conceptualization of context as “a static, non-changeable boundary condition” (page 4) [37]. Instead they recommend distinguishing between ‘omnibus context’, describing the overall setting in which the intervention takes place and which typically are difficult to change, and the ‘discrete context’ which refers to specific individual, leader, group and organizational aspects directly relevant to the implementation and change process, and which in principle can be changed and should be a target for change.

Based on these three approaches we will focus on answering the following questions:To what degree was the intervention implemented as planned? (e.g. were two workshops per department conducted? Were action plans developed?)How did the workshop-participants and all employees at the participating departments perceive the intervention? (Here we will particularly focus on if employees felt that improvement suggestions were meaningful, and if they were involved in the implementation of the improvement suggestions.)Did the mental models of the participants have an influence on the implementation process (e.g. employees’ expectation that use of assistive devices can be increased in the department)?Did context aspects (omnibus and discrete context) have an influence on the implementation, and if yes, in which way and how it was handled?

Our data sources consist of qualitative and quantitative measures including three questionnaire surveys (before (baseline), during (follow-up I) and after the intervention (follow-up II)), detailed notes from the two workshops in each department, project documentation about activities and materials delivered to the intervention departments and implementation status documentation (once a month after workshop 2). While all of these measures will be conducted in all intervention departments, a more detailed qualitative assessment is only possible in selected departments due to budget restraints. Based mainly on information from the monthly implementation status documentation, two departments with a high level, and two departments with a low level of implementation will be selected for focus group interviews with employees, which will be conducted after the end of the intervention period. In these departments employees will be asked to elaborate on the implementation process and why implementation succeeded or did not succeed.

The methods for the process evaluation will be developed continuously during the project period to enable us to focus on unforeseen implementation challenges or aspects we wish to assess further. Thus, the final process evaluation may divert somewhat from the present evaluation plan (e.g. total number of interviews) or methods used.

### Blinding

Due to the interventional trial design, participants and researchers managing the workshops cannot be blinded to group allocation. However, outcome assessors and quantitative data analysts will be blinded to group allocation.

### Outcome measures

Outcomes are objectively measured by digital push-button counters and by accelerometers at baseline and 1 year follow-up, and by questionnaire survey at baseline, after 6 months and at 1 year follow-up.

#### Primary outcome measure

The primary outcome is the use (at department level) of assistive devices during the entire 1 year follow-up adjusted for the use at baseline (4 weeks prior to the intervention). The use (frequency and total amount) of assistive devices (i.e. lifts, sliding sheets or patient transporters) is measured continuously during the entire project-period with digital push-button counters. Two digital push-button counters will be placed next to the doorframe of the exit door in each patient room. The healthcare workers are encouraged to push one of the following two buttons every time they leave the room after having performed patient transfer; button 1 (green) which is labelled with *“Press this button if you used the necessary assistive devices for your patient transfer”* and button 2 (red) which is labelled with *“Press this button if you did not use the necessary assistive devices for your patient transfer”*. The ratio between the number of Button 1 counts and the total number of counts (Button 1 + 2) will be calculated for each set of counters and used as the primary outcome. To increase the employees’ motivation for pressing the buttons, frequent motivational emails to all participants, telephone calls to the departments and occasional personal attendance will be administered throughout the study period.

#### Secondary outcome measures

Secondary outcome measures are: 1) objectively measured use of assistive devices using accelerometers (at the department level), and by questionnaire (at the individual level accounting for cluster), the change from baseline to 1 year follow-up in 2) musculoskeletal pain intensity during the last week (back, neck and shoulder), 3) perceived physical exertion during work, 4) occurrence of work-related back injuries during patient transfer, 5) work ability, 6) social capital, 7) knowledge on how to perform proper patient transfer, and 8) organizational readiness to change. To measure short-term effects the questionnaire will also be distributed after 6 months. During each questionnaire round, participants with non-response will receive up to two reminders to reply.

Besides using pushbuttons for measuring the use of assistive devices we will also measure the use (frequency and total amount) of assistive devices (i.e. lifts or patient transporters) with accelerometers (Actigraph, Florida, US), normalized to the number of employees with patient transfer in each department. The accelerometers will measure the movement of the assistive device, and will be discretely placed on patient transporters/lifts for periods of three weeks at baseline, and at 1 year follow-up. The use of sliding pieces and other disposable assistive devices will not be measured using accelerometers in this study. Using questionnaires, the use of assistive devices will, furthermore, be obtained by asking: *“Do you transfer patients without the necessary assistive devices? (Think of situations where you should have used assistive devices)”*. Subjects will reply on a 5-point scale: 1) “0 out of 4 transfers (i.e. almost never)”, 2) “1 out of 4 transfers”, 3) “2 out of 4 transfers”, 4) “3 out of 4 transfers” and 5) “4 out of 4 transfers (i.e. every time)”.

Pain intensity in the lower-back will be rated subjectively using a 0–10 modified visual analog scale, where 0 indicates “no pain at all” and 10 indicates “worst pain imaginable” [39, 40]. Drawings from the Nordic questionnaire for the analysis of musculoskeletal symptoms are used to define the body regions of interest [41].

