### Participants

In April 2016, 27 departments (clusters) with 642 healthcare workers located at five different Danish community hospitals were allocated to a participatory intervention or a control group. The inclusion criteria were departments with healthcare workers working with daily patient transfer. Baseline characteristics of employees belonging to the 14 departments in the intervention group and to the 13 departments in the control group are presented in Table 1.

**Table 1 Tab1:** Characteristics of the two groups. Values are presented as numbers, percentage and mean (SD) from the participants who answered the baseline questionnaire

	Intervention	Control
Departments (N)	14	13
Employees (N)	324	318
Women (N)	289	285
Men (%)	12	12
Age (years)	43 (12)^a^	40 (12)
Height (cm)	169 (7)	170 (7)
Weight (kg)	70 (15)	71 (14)
BMI (kg∙m^-2^)	24 (4.6)	25 (4.4)

^a^ difference between groups at baseline, *P* < 0.05

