### Statistical analysis

All statistical analyses will be performed using the SAS statistical software for Windows (SAS Institute, Cary, NC). For the primary outcome, use of assistive devices during the entire 1-year follow-up will be evaluated using linear mixed models. Analyses will be adjusted for use of assistive devices during baseline. Cluster is entered in the model as a random factor. We will perform all statistical analyses in accordance with the intention-to-treat principle using a linear mixed model, which inherently accounts for missing values. An alpha level of 0.05 will be accepted as significant. Outcomes will be reported as between-group least mean square differences and 95% confidence intervals from baseline to follow-up.

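### The continuous questionnaire outcomes are compared as change from baseline with no stated adjustment for their own baseline value, which gives away precision at no benefit

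*Protocol article*

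**What the plan says.** The Secondary outcome measures section lists eight items. Device use, by accelerometer and by questionnaire, is item 1. The remaining items are introduced as "the change from baseline to 1 year follow-up in 2) musculoskeletal pain intensity during the last week (back, neck and shoulder" and continue with exertion, back injury, work ability, social capital, knowledge and readiness to change. Back injury is asked as an occurrence and is not a continuous score, so the point here concerns the other six. The Outcome measures section says these data are collected "by questionnaire survey at baseline, after 6 months and at 1 year follow-up". The baseline survey went out in February 2016 and randomization took place in April 2016, so every baseline value precedes allocation.

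The Statistical analysis section begins with the primary outcome: "use of assistive devices during the entire 1-year follow-up will be evaluated using linear mixed models". The next sentence reads "Analyses will be adjusted for use of assistive devices during baseline". Department is then named as a random factor, and all analyses are to follow intention-to-treat "using a linear mixed model, which inherently accounts for missing values". Results are reported thus: "Outcomes will be reported as between-group least mean square differences and 95% confidence intervals from baseline to follow-up". The Primary outcome measure section confirms that device use over follow-up is adjusted for device use at baseline. No sentence says the same of any questionnaire score.

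**The concern.** The protocol adjusts its primary outcome for that outcome's baseline but states its continuous questionnaire outcomes as plain change. Subtracting the baseline gives it a weight of one, whereas the weight that minimises residual variance is the regression slope, which equals r when the variances at the two times are equal. Over-weighting the baseline has two effects. Standard errors are larger than the collected data require. And if the arms differ by chance at baseline, the change comparison over-corrects: the arm that starts worse is expected to improve more merely through regression to the mean. With 27 departments as the units randomized, chance imbalance in a score is quite possible.

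**Working it through.** **The protocol's own figure.** The only planned size is for the primary outcome: 13 clusters per group for 95% power, SD 10%, difference 15%, α = 0.05 (taken as two-sided). The normal approximation gives n = 2 × (1.960 + 1.645)² × (10/15)² = 11.6, so 12 per group. The two-sample t-test has power 93.9% at 12 and 95.6% at 13 per group, so 13 reproduces. It is untouched by what follows. The protocol gives no precision figure for the questionnaire outcomes.

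**Participant-level precision.** Scale the score to variance 1 at both times, with correlation r (assumed; not in the protocol).
- Unadjusted change: variance 1 + 1 − 2r = 2(1−r).
- ANCOVA on the outcome's own baseline: residual variance 1 − r² = (1−r)(1+r).
- Ratio, change to ANCOVA: 2/(1+r).
- Given a chance baseline difference d between arms, the expected change difference is the true effect minus (1−r)d. ANCOVA removes this term.

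| r | 2(1−r) | 1−r² | Variance ratio | SE ratio | Carry-over of d |
|---|---|---|---|---|---|
| 0.3 | 1.40 | 0.91 | 1.54 | 1.240 | 0.70 |
| 0.5 | 1.00 | 0.75 | 1.33 | 1.155 | 0.50 |
| 0.7 | 0.60 | 0.51 | 1.18 | 1.085 | 0.30 |
| 0.8 | 0.40 | 0.36 | 1.11 | 1.054 | 0.20 |

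**Department-level variance.** Let each department of m responders (642/27 = 23.8 on average at baseline) add a term D common to both analyses. The ratio becomes [D + 2(1−r)/m] / [D + (1−r²)/m], which is nearer 1. For illustration, if D equals the ANCOVA participant term at r = 0.5, that is 0.75/m, the ratio falls from 1.33 to (0.75 + 1.00)/(0.75 + 0.75) = 1.17. D is not given either.

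**Does the loss depend on how change is modelled?** Change might be a per-person difference or an arm-by-time contrast in a three-wave mixed model. The variances below are for the 1-year contrast, multiplied by the total number of participants. They assume equal correlation between waves, data missing completely at random, 6-month and 1-year response independent and equally likely, and no clustering.

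| r | Retention per wave | Per-person change, complete cases | Three waves, free baseline means | Three waves, common baseline mean | ANCOVA, complete cases |
|---|---|---|---|---|---|
| 0.5 | 65% | 6.154 | 5.497 | 4.497 | 4.615 |
| 0.5 | 80% | 5.000 | 4.683 | 3.683 | 3.750 |
| 0.7 | 65% | 3.692 | 3.375 | 3.015 | 3.138 |
| 0.7 | 80% | 3.000 | 2.840 | 2.480 | 2.550 |

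- Per-person change against three waves with a common mean: 1.21 to 1.37.
- Free against common baseline means: 3.375/3.015 = 1.12 to 4.683/3.683 = 1.27. The loss therefore remains under the repeated-measures reading unless the baseline means are constrained.
- ANCOVA against three waves with a common mean: 3.750/3.683 = 1.02 to 3.138/3.015 = 1.04. Most of the gain comes from using the baseline properly.

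**The case against.** The protocol is a condensed article, and covariates for secondary outcomes are commonly left to an analysis plan. Defining an outcome as change does not forbid a baseline covariate: change regressed on baseline gives the same arm difference as the follow-up value regressed on baseline. The reporting sentence also covers the primary outcome, which is adjusted, so it does not by itself rule adjustment out. A change comparison is unbiased under randomization, and the regression-to-the-mean point matters only given a chance imbalance. At r = 0.8 the standard error is only about 5% larger. All of this stands and limits the point to a modest one. It does not remove it, because the protocol does state the comparison it intends for these outcomes and states baseline adjustment only for the primary.

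Three stronger readings are tempting and are not supported.
- **That incomplete responders are dropped, so that "which inherently accounts for missing values" is false.** This would follow if a per-person difference were the dependent variable; at an assumed retention of 65% to 80%, 642 × 0.35 = 225 to 642 × 0.20 = 128 people would be lost. The text never says so. Three waves, intention-to-treat and a mixed model fit a repeated-measures contrast equally well, and that contrast keeps partial responders. Only department is named as a random factor, so the text confirms neither model.
- **That baseline device use is the covariate for pain and the other scores.** The sentence directly follows the primary-outcome sentence and repeats the primary-outcome definition, so it most naturally belongs there.
- **That age must be adjusted for because Table 1 flags it (43 v 40 years) as a "difference between groups at baseline".** Allocation was random, and a significant baseline test does not show that age predicts any of these outcomes.

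**Conclusion.** The point holds as a free improvement to the secondary analyses. As stated, the six continuous questionnaire outcomes are compared as change without adjustment for their own baseline, which costs participant-level variance by a factor of 1.54, 1.33 or 1.11 at r = 0.3, 0.5 or 0.8. The direction is certain at participant level for any r below 1 with equal variances at the two times. The size is not, since r is assumed and department-level variance, also unknown, reduces the gain. Nothing here affects the primary outcome, its model or the 13 clusters per group, and the protocol's comparison is inefficient, not invalid. On missing data, what can be said is that the assumption behind the mixed model should be named, not that responders are lost.

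**What to change.** For each continuous questionnaire outcome, state one of two analyses and report the arm difference at 1 year with its 95% confidence interval:
- a linear mixed model for the 1-year value with the outcome's own baseline as covariate and department as a random effect; or
- a linear mixed model for the baseline, 6-month and 1-year values with a common baseline mean in both arms and random department and participant effects.

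The second also lets participants with a missing wave contribute; under the assumptions above it is 2% to 4% better in variance than the first. The result may still be described as a difference in change. Replace the phrase about missing values with a statement that the model gives valid results if data are missing at random given the values included in it.

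The cost is wording in the analysis section or analysis plan. Every variable is already collected, and no change to the sample size, visits or primary analysis is needed.

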### Sample size

The sample size calculation was based on the primary outcome. A priori power analysis based on previous measurements revealed that 13 clusters in each group (26 departments in total) for 95% power, SD of 10% and a minimal relevant group-difference in the use of assistive devices of 15%, is sufficient to test the null-hypothesis of equality (α = 0.05).

### Statistical analysis

All statistical analyses will be performed using the SAS statistical software for Windows (SAS Institute, Cary, NC). For the primary outcome, use of assistive devices during the entire 1-year follow-up will be evaluated using linear mixed models. Analyses will be adjusted for use of assistive devices during baseline. Cluster is entered in the model as a random factor. We will perform all statistical analyses in accordance with the intention-to-treat principle using a linear mixed model, which inherently accounts for missing values. An alpha level of 0.05 will be accepted as significant. Outcomes will be reported as between-group least mean square differences and 95% confidence intervals from baseline to follow-up.

### Adverse events

Although this is an organizational intervention, adverse events in relation to participation in the project will be registered with an open-ended question at the questionnaire at 6 months and 1 year follow-up. The question will be *“Have you experienced any adverse events – physical, mental or other - in relation to your participation in the project”*.

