### Phase 2: participatory intervention

A characteristic feature of participatory ergonomic interventions is the formation of a problem solving team, which is given ownership and insight of the challenges at hand that need to be solved [19]. The current intervention will consist of two two-hour workshops where the problem solving team consisting of selected employees (nurses, nursing aides and porters), leaders and the hospital’s health and safety consultants will be asked to develop and implement an action plan consisting of multiple solutions to increase the use of assistive devices in their department (at cluster level) (Fig. 2 - Phase 2). The main aim of the first workshop is to kick-start the participatory process by: a) letting the participants brainstorm on barriers and potential solutions for improving the use of assistive devices, and b) subsequently develop a simple action plan for implementing one of these solutions. Approximately two weeks before workshop I, employees in intervention departments will receive a report via e-mail. The report summarizes selected results of the baseline questionnaire in order to provide employees and their department leaders with information about specific challenges with regard to the use of assistive devices in their department. Based on discussions of the report and presentation of barriers and potential solutions collected through the aforementioned interviews and analysis of “best practice”, participants will then be asked to identify and discuss potential solutions for increasing the use of assistive devices at the department. The workshop participants are then asked to select one achievable solution and implement it over the course of the following weeks. Approximately 3 months after the first workshop all departments will be invited to a second and final workshop. The aims of workshop II is twofold: a) to discuss the status and experiences with the implementation of the solution developed in workshop I, and b) develop an action plan for the implementation of 1–5 additional solutions. The decision about which suggestions to choose should be based on what workshop participants are most motivated for, and which are considered to have the largest effect on improving the use of assistive devices in the 6–9 months after workshop II.

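### The adverse-event question depends on staff linking an event to project participation and has no recall window, so its counts are not like for like between arms; harms outside the listed outcomes have no arm-neutral measure

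*Protocol article*

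**What the plan says.** Under Adverse events, the protocol article says that events connected with taking part will be "registered with an open-ended question at the questionnaire at 6 months and 1 year follow-up". The item is worded: "Have you experienced any adverse events – physical, mental or other - in relation to your participation in the project". It is the only item labelled adverse events. No recall period is stated, and no restriction to one arm.

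Four other sections bear on how staff will read it:

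- **Blinding:** "participants and researchers managing the workshops cannot be blinded to group allocation". Study design and randomization adds that departments were told their allocation by email straight after randomization.
- **Control group:** the 13 control departments "will not receive any intervention, and will be encouraged to continue their normal working procedures throughout the study period".
- **Phase 2:** the workshops are for "the problem solving team consisting of selected employees (nurses, nursing aides and porters"), together with leaders and safety consultants. Their action plan is to contain "multiple solutions to increase the use of assistive devices in their department (at cluster level").
- **Primary outcome measure:** push-button counters are supported by "frequent motivational emails to all participants, telephone calls to the departments and occasional personal attendance will be administered throughout the study period".

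Secondary outcome measures lists back injury during patient transfer, musculoskeletal pain, exertion and work ability. None of these items mentions the project.

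**The concern.** A harm item can be compared between randomized arms only if both arms face the same question in practice. Here the respondent decides on causality first, and an event judged unrelated is never written down, so analysis cannot recover it. What there is to relate an event to is not the same in the two arms.

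Two opposite errors are possible. The intervention arm can show more events with no true difference, because it has more project activity to blame. Or real harm from changed ward routines can go unreported by staff who never attended a workshop and do not think of themselves as having taken part. With no recall window, an answer at 1 year may also repeat one given at 6 months.

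**Working it through.** The documents give no figure for this item, so there is nothing to reproduce. The article's only calculation (13 clusters per group) concerns the primary outcome and plays no part here. The check is a comparison of sections, followed by illustrations.

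**1. What participation covers, by group**

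| Group | Project contact described |
|---|---|
| Control staff | Questionnaires, push-buttons, motivational contacts; no intervention |
| Intervention staff not attending workshops | The same, plus the emailed department report and department-wide changes |
| Workshop attendees | All of this, plus workshops and the action plan |

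The article uses the word in two senses. Recruitment counts everyone who answered the baseline questionnaire as a participant (642). Phase 2 speaks of voluntary participation in the workshops, with written consent. A respondent could reasonably read the item either way. The back-injury item, by contrast, fixes a 12-month window and needs no link to the project.

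**2. Effect of unequal attribution (illustration)**

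Inputs from the Abstract and Table 1: 324 intervention and 318 control staff. Assumed: the same true event rate in both arms, the attribution proportions shown, and complete follow-up. Expected reports = staff × event rate × attribution, rounded to whole numbers. The p-values are Fisher's exact test and ignore clustering.

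| True rate, both arms | Attribution, intervention / control | Reports | p |
|---|---|---|---|
| 10% | 50% / 0% | 324 × 0.10 × 0.50 = 16.2, so 16 vs 0 | 0.00003 |
| 10% | 50% / 10% | 16 vs 318 × 0.10 × 0.10 = 3.2, so 3 | 0.004 |
| 10% | 50% / 25% | 16 vs 318 × 0.10 × 0.25 = 8.0, so 8 | 0.14 |
| 5% | 50% / 0% | 324 × 0.05 × 0.50 = 8.1, so 8 vs 0 | 0.007 |
| 2% | 50% / 0% | 324 × 0.02 × 0.50 = 3.2, so 3 vs 0 | 0.25 |

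A spurious excess needs a marked attribution gap and events that are not rare. It does not need complete silence in the control arm.

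**3. Under-reporting by non-attenders (illustration)**

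Respondents per intervention department: 324/14 = 23.1. The article gives no number of attendees. If 4 to 8 per department attended, and only they felt the item applied to them, the share of staff in a position to report would be 4 × 14/324 = 17% to 8 × 14/324 = 35%. This is an extreme case, because it assumes that no non-attender reports anything.

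**4. What the unattributed outcomes can show**

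The Discussion puts annual back-injury incidence below 4%. Taking 4% in controls, two-sided α = 0.05 and full follow-up, 80% power for the comparison of 318 with 324 staff requires a rise to about 9.6% with no clustering, 11.2% with a design effect of 1.5, and 12.7% with a design effect of 2. The design effects are assumed, since no intracluster correlation is given. A randomized comparison for this harm therefore exists, but only a large increase would be seen.

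**The case against.** The strongest reply is that a reader might infer that the arms cannot be compared for harm at all, and the documents contradict that. Back injury, pain in back, neck and shoulder, exertion during transfer and work ability are asked in both arms without reference to the project, and the Statistical analysis section plans between-group differences with confidence intervals. These cover the most foreseeable physical harms of changed transfer routines. This stands, and it limits the point to other harms.

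It may also be tempting to say that control staff and most intervention staff have almost nothing to report. That is inference. Controls meet the counters, the contacts and the questionnaires. Non-attenders receive the department report and are to hear the action plan at department meetings. Without attendance numbers, the word most cannot be checked. This stands too.

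Third, the Adverse events section promises registration, not a test between arms, so there is no contradiction in the plan, and the scenarios rest on assumed inputs. Agreed. But the wording is printed in full, so the dependence on attribution is a stated choice and not a detail left to another document. Descriptive counts shown by arm would still invite a comparison that they cannot bear. The missing window is a weaker complaint: free text may reveal repeats, and the full questionnaire may set a period.

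**Conclusion.** The point holds in a limited form. The adverse-event item filters reports through the causal judgement of unblinded staff, and that filter differs between arms and, within intervention departments, between attenders and others. Its counts are not like for like and may miss events that staff do not attribute to the project. The consequence is confined to physical, mental or organizational harms outside the listed secondary outcomes, which have no arm-neutral measure.

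The size cannot be established from the documents. The scenarios run from a strong spurious excess (16 vs 0) to nothing notable (3 vs 0, or 16 vs 8), depending wholly on assumed event and attribution rates, and they ignore clustering and loss to follow-up. This is a worthwhile, inexpensive improvement in harm ascertainment. It is not an error that affects the primary analysis.

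**What to change.** In each questionnaire round still to come, ask all staff in both arms whether they have had any physical, mental or other adverse event at work within a fixed window, with free text as now. Follow with a tick box asking whether they think it was related to the project. Report the first question by arm, allowing for cluster, and keep the attribution answer as descriptive.

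The window must fit the rounds that remain. If both remain, use 6 months at each. The intervention began in April 2016 and the article appeared in December 2016, so the 6-month round has probably passed. If only the 1-year round remains, the window should cover the whole intervention year (12 months), because a 6-month window would leave the first half uncovered.

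The cost is one reworded item and one tick box, plus more unrelated free-text events to code. A 12-month window also asks for longer recall, as the existing back-injury item already does.
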